### Study design and statistical considerations

The aim of the OGSG1602 phase II study is to assess the efficacy of panitumumab as first-line therapy for patients with WT RAS CRC who are not eligible for intensive chemotherapy. Therefore, we decided that the primary endpoint is the DCR and secondary endpoints are PFS, OS, response rate, time to treatment failure, and the incidence of grade 3/4 toxicities. The DCR is assessed by best response. An independent review committee assess efficacy. Based on the AVEX trial and the Spanish phase II study conducted by Sastre et al., the null hypothesis is “DCR is 45%,” and the alternative hypothesis is “DCR is >70%” [10, 11]; this will be assessed using an exact *p*-value of 0.05 and a power of 0.90 based on the Clopper-Pearson method. Thus, the sample size is 33. The total sample size is set to 36 to account for deviation. More than 22 events of DCR are needed for rejecting the null hypothesis. All statistical analyses will be conducted at the OGSG Data Center.

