### Endpoints

#### Primary endpoint

The primary endpoint is to determine the disease control rate (DCR), defined as a proportion of best overall response of complete response (CR), partial response (PR), or stable disease (SD). Response will be assessed based to the Response Evaluation Criteria in Solid Tumors (RECIST) version 1.1 [16].

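### Thirty-three patients give power 0.84, not 0.90, under the exact test named; sample size, sidedness, cut-off, size and power need restating together

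*Protocol article*

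**What the plan says.** The design is a single-arm phase II trial. The primary endpoint is the DCR, "defined as a proportion of best overall response of complete response (CR), partial response (PR), or stable disease (SD").

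Under Study design and statistical considerations, the protocol article sets a null DCR of 45% and an alternative above 70%. On the test it says "this will be assessed using an exact *p*-value of 0.05" and "a power of 0.90 based on the Clopper-Pearson method". It then concludes "Thus, the sample size is 33. The total sample size is set to 36 to account for deviation". The decision rule is "More than 22 events of DCR are needed for rejecting the null hypothesis".

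The section does not say whether 0.05 is one-sided or two-sided, or whether the rule refers to 33 or 36 patients.

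**The concern.** Method, significance level, power, sample size and decision rule are all printed, so they can be checked against each other without any other source. Under the exact method named, 33 patients do not deliver the stated power. The decision rule does not belong to 33 patients either.

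This is the only primary analysis. If 33 patients are analysed, as the text plans for, the chance of missing a true DCR of 70% is 0.16 rather than 0.10. The three patients described as a margin are then needed to reach the stated power, and even that holds only for a one-sided test. A reader who applies the printed rule literally gets a different power again.

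**Working it through.** **Inputs**, all from Study design and statistical considerations: null DCR 0.45; alternative 0.70 (printed as above 70%, with 0.70 as the design point); exact test at 0.05; power 0.90; 33 required; 36 enrolled; rejection at more than 22.

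**Formulas.** For n patients and rejection at r or more:

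- size = Σ (x = r to n) C(n,x) · 0.45^x · 0.55^(n−x)
- power = Σ (x = r to n) C(n,x) · 0.70^x · 0.30^(n−x)

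The exact cut-off is the smallest r with size ≤ 0.05 (one-sided), or ≤ 0.025 in the upper tail (two-sided 0.05). This is the same as asking that the Clopper-Pearson lower limit exceed 0.45.

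**Step 1: can 33 with power 0.90 be reproduced?**

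| n = 33, reject at | size | power |
|---|---|---|
| ≥ 20 | 0.0522 | 0.912 |
| ≥ 21 | 0.0242 | 0.839 |
| ≥ 22 | 0.0100 | 0.733 |
| ≥ 23 | 0.0036 | 0.599 |

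No row has both size ≤ 0.05 and power ≥ 0.90. The exact cut-off is 21. Because 0.0242 is below 0.025 as well as 0.05, it is the same cut-off for either sidedness: the lower limit of the two-sided 95% interval at 21/33 is 0.451, just above 0.45. At 20/33 even the one-sided 95% lower limit is 0.448, below 0.45. Power is therefore 0.839, and type II error is 1 − 0.839 = 0.161.

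Two other routes come to 33:

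- The one-sided arcsine approximation: ((1.645 + 1.282) / (2(asin√0.70 − asin√0.45)))² = 32.7, rounded up to 33.
- The exact calculation with the cut-off of 20 accepted, that is, with size 0.052 treated as 0.05.

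The first is not the method named. The second exceeds the stated level.

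**Step 2: smallest n with power ≥ 0.90, one-sided 0.05.**

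| n | reject at | size | power |
|---|---|---|---|
| 33 | ≥ 21 | 0.0242 | 0.839 |
| 34 | ≥ 21 | 0.0368 | 0.890 |
| 35 | ≥ 22 | 0.0255 | 0.865 |
| 36 | ≥ 22 | 0.0382 | 0.908 |
| 37 | ≥ 23 | 0.0268 | 0.887 |
| 38 | ≥ 23 | 0.0394 | 0.924 |

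The first n to reach 0.90 is 36. Losing one, two or three patients from the analysis takes power to 0.865, 0.890 or 0.839.

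**Step 3: two-sided 0.05.** At n = 36 the cut-off is ≥ 23 (upper-tail size 0.0175, power 0.837). The smallest n reaching 0.90 is 42, with rejection at ≥ 26 (upper-tail size 0.0205, power 0.903).

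**Step 4: the printed rule.** More than 22 is literally 23 or more.

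| Reading of the rule | n = 33: size, power | n = 36: size, power |
|---|---|---|
| ≥ 23 (literal) | 0.0036, 0.599 | 0.0175, 0.837 |
| ≥ 22 | 0.0100, 0.733 | 0.0382, 0.908 |

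Only 36 analysed with rejection at 22 or more reaches 0.90. That is neither the stated sample size nor the literal rule.

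**The case against.** The best defence is that the trial enrols 36, and that 36 analysed in a one-sided test with rejection at 22 or more give size 0.038 and power 0.908. The text does not say that patients with deviations leave the denominator, so the analysed number may never fall to 33. Type I error is not inflated under any reading of the printed rule. This stands, and it limits the consequence: the fault is a misdescribed power statement. A reader might infer that the trial as enrolled cannot reach its stated power, or must enrol more; the document does not support that, because it leaves open a one-sided test on all 36.

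A second defence is that the alternative is printed as above 70%, and that 33 patients come close to 0.90 at a slightly higher rate: with the cut-off at 21, power is 0.895 at a true DCR of 72% and 0.917 at 73%. That is correct, and it shows that the shortfall is small in effect-size terms. But 70% is the only value given for the calculation, and at that value power is 0.84.

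Two other readings are tempting. One is that 36 is simply the minimum. That holds only for a one-sided 0.05 test, and sidedness is not stated. The other is that 33 came from the arcsine formula. The document mentions no approximation, and accepting the cut-off of 20 with size 0.052 leads to 33 just as well, although that cut-off does not match the printed rule. The origin cannot be determined.

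**Conclusion.** The statement that 33 patients give power 0.90 is wrong as printed. At a DCR of 70%, exact power is 0.84, about 6 percentage points lower, and type II error is about 1.6 times the stated value (0.161/0.10). This does not depend on sidedness; it rests only on the printed 45%, 70% and 0.05 and on an exact test that keeps its size at or below 0.05.

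What follows for the 36 enrolled does depend on sidedness. One-sided, 36 reach 0.908 only with all 36 analysed and rejection at 22 or more, so there is no reserve. Two-sided, 36 give 0.837.

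The printed rule adds a separate inconsistency. Taken literally it is the exact two-sided cut-off for 36 patients, with power 0.837; it is not the exact cut-off for 33 on either sidedness.

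**What to change.** Keep enrolment at 36, delete the statement that 33 gives 0.90, and replace the sample-size sentences and the decision rule with one consistent set. Either:

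- one-sided exact test at 0.05, all 36 enrolled patients in the denominator, reject at 22 or more, size 0.038, power 0.908, no allowance for exclusions; or
- 33 patients analysed, exact test, reject at 21 or more, size 0.024, power 0.84.

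In both cases state the sidedness, and say that the cut-off will be recomputed exactly if the number analysed differs from the planned one. Changing the sample-size figures alone is not enough: power 0.908 printed beside a rule of more than 22 events would still conflict with the 0.837 that the rule gives with 36 patients.

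The cost is a few sentences of text. Neither option changes enrolment. If a two-sided test with power 0.90 is intended, 36 will not provide it; the text should then report 0.837 at 36 (reject at 23 or more) or the target would have to rise to 42.

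### The rejection rule of more than 22 disease-control patients does not give the stated power of 0.90: exact power at a DCR of 70% is 0.84 with 36 analysed and 0.60 with 33

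*Protocol article*

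**What the plan says.** All the relevant statements are in the protocol article, section Study design and statistical considerations.

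- Hypotheses: "the null hypothesis is “DCR is 45"%, and "the alternative hypothesis is “DCR is >70"%.
- Error rates and method: an exact p-"value of 0.05 and a power of 0.90", with the Clopper-Pearson method named as the basis.
- Size: "Thus, the sample size is 33". Then: "The total sample size is set to 36 to account for deviation".
- Decision rule: "More than 22 events of DCR are needed for rejecting the null hypothesis".

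The section does not say whether the 0.05 is one- or two-sided. It does not say whether the count refers to 33 or 36 patients.

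**The concern.** A null rate, an exact level and a number analysed together determine the critical count, and that count with the alternative rate determines the power. The article gives all of these figures, so they can be checked against each other, and they do not agree.

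This count is the only rejection threshold given for the primary endpoint. If it differs from the exact test in the same paragraph, some results are significant by the test but not by the count. With denominator and sidedness left open, the choice between the two could be made after the data are known. The counts affected are 21 or 22 of 33 (64% or 67%) and 22 of 36 (61%). They lie not far below the 70% target, so such results are plausible.

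**Working it through.** **Inputs**, all from Study design and statistical considerations: p0 = 0.45; p1 = 0.70 (the alternative is written as above 70%, so power is taken at that boundary); level 0.05; power 0.90; n = 33 calculated and 36 enrolled; rule X > 22, that is X ≥ 23. Sidedness is not given, so both versions are worked.

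**Step 1. The plan's own n = 33.** The text attributes the figure to the exact method: "a power of 0.90 based on the Clopper-Pearson method". The exact method does not reproduce it (step 2). Approximate one-sided formulas come close:

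- Normal: n = [(1.645·√(0.45·0.55) + 1.282·√(0.70·0.30)) / 0.25]² = 31.6, so 32.
- Arcsine: n = [(1.645 + 1.282) / (2·(asin√0.70 − asin√0.45))]² = 32.7, so 33.

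Of the variants tried, only the one-sided arcsine approximation gives 33. The two-sided versions give 40 and 41.

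**Step 2. Exact critical counts.** For a cutoff r, alpha = P(X ≥ r | n, 0.45) and power = P(X ≥ r | n, 0.70). A one-sided 0.05 test takes the smallest r with upper tail ≤ 0.05. A two-sided 0.05 test by Clopper-Pearson takes the smallest r with upper tail ≤ 0.025.

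| Analysed | Rule | Upper tail at 45% | Power at 70% | Status |
|---|---|---|---|---|
| 33 | ≥20 | 0.0522 | 0.912 | misses 0.05 |
| 33 | ≥21 | 0.0242 | 0.839 | cutoff, one- and two-sided |
| 33 | ≥22 | 0.0100 | 0.733 | loose reading of the rule |
| 33 | ≥23 | 0.0036 | 0.599 | rule as written |
| 34 | ≥21 | 0.0368 | 0.890 | cutoff, one-sided |
| 34 | ≥23 | 0.0065 | 0.693 | rule as written |
| 35 | ≥22 | 0.0255 | 0.865 | cutoff, one-sided |
| 35 | ≥23 | 0.0109 | 0.773 | rule as written; also two-sided cutoff |
| 36 | ≥22 | 0.0382 | 0.908 | cutoff, one-sided |
| 36 | ≥23 | 0.0175 | 0.837 | rule as written; also two-sided cutoff |

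The literal rule stays below 0.90 at every number analysed from 33 to 36.

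**Step 3. Check through Clopper-Pearson limits.** For 22/36 the 90% interval is 46.0% to 74.7%, which excludes 45%. The 95% interval is 43.5% to 76.9%, which includes it. For 23/36 the 95% lower limit is 46.2%. For 21/33 and 22/33 the 95% lower limits are 45.1% and 48.2%, and both exclude 45%. This agrees with the table.

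**Step 4. Sample size that does reach 0.90.** One-sided, the smallest n with exact power of at least 0.90 is 36 (≥22). Two-sided, it is 42 (≥26, power 0.903).

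**Step 5. How often test and rule disagree at a true DCR of 70%.** With 36 analysed and a one-sided test, the only such count is 22: 0.9083 − 0.8373 = 0.071. With 33 analysed and either sidedness, the counts are 21 and 22: 0.8387 − 0.5993 = 0.239.

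**The case against.** The strongest defence is that the error is one of wording. At least 22 of 36, one-sided, meets both the 0.05 and the 0.90, and 36 is the smallest number that does so exactly. The cutoff sentence directly follows the one that sets the total at 36. On that view, one loose phrase in a condensed article is the whole problem. This is probably the right explanation of the cutoff. It does not cure the text, which says more than 22 and presents 33 as the calculated size, with 36 as an allowance for deviation.

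Three stronger readings are tempting, and the document supports none of them.

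- *The cutoff fits neither sample size.* This would need a stated one-sided test. One-sided testing is only inferred from the upward alternative. Under two-sided 0.05 Clopper-Pearson, 23 is exactly the critical count at 36, and the defect there is the power of 0.837.
- *The rule by itself takes power from 0.90 to 0.60.* At 33, the best valid cutoff gives 0.839, so that part of the loss comes from the sample size. The rule accounts for the further drop from 0.839 to 0.599, and only if all three reserve patients are lost and the cutoff is not adjusted.
- *False positives are more likely.* They are not. The literal rule has an upper tail of 0.0175 at 36 and 0.0036 at 33. The risk is a false negative.

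It also stands that the exposure is narrow if all 36 are analysed: one count, with probability 0.071 at a DCR of 70%.

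An article may leave detail to the full protocol or SAP. Here, however, it prints a numerical rule that conflicts with the test and power printed beside it.

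**Conclusion.** The point holds as an internal contradiction in the primary decision rule. As written, the rule gives exact power of 0.837 with 36 analysed and 0.599 with 33, against a stated 0.90. At 33 it is two patients too strict under either sidedness. At 36 it is one patient too strict if the test is one-sided, and correct for a two-sided test whose power is then misstated. Separately, 33 patients do not give 0.90 by the exact method; they give 0.839.

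These results assume a true DCR of exactly 70%, a null of 45%, and a fixed cutoff of 23 whatever the number analysed. That one-sided testing with at least 22 of 36 was intended is an inference from the figures and is not stated in the article.

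**What to change.** State the sidedness, the denominator and "at least" in place of more than, and settle this before the primary results are known. Two versions are consistent:

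- **(a) One-sided exact 0.05.** Reject if at least 22 of 36 have disease control (alpha 0.038, power 0.908 at 70%). Give cutoffs of 21, 21 and 22 for 33, 34 and 35 analysed, with power 0.839, 0.890 and 0.865. Report the matching 90% Clopper-Pearson interval, because the 95% interval for 22/36 includes 45%.
- **(b) Two-sided 0.05.** Keep at least 23 of 36 and restate power as 0.84. Tie the cutoff to the number analysed: by Clopper-Pearson it is 21, 22 and 23 for 33, 34 and 35, with power 0.839, 0.807 and 0.773.

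In either case, correct the statement that 33 patients give power 0.90 under the exact method. They give 0.84, and 36 is the smallest number that reaches 0.90 one-sided. Under (a), 36 therefore holds no reserve: losing one to three patients from the analysis brings power below 0.90.

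The cost is wording in the protocol and SAP, with no extra patients. Only a wish to keep 0.90 with a two-sided test would need more (at least 42).

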### Monitoring

The Data and Safety Monitoring Committee (DSMC) of the OGSG will independently review the efficacy and safety data obtained from the present study. On the basis of monitoring, the DSMC will consider the early termination of a treatment regimen during the study and a modification of the study protocol. Protocol compliance, safety, and on-schedule study progress will also be monitored by the DSMC. The monitoring will be performed annually.

## Discussion

The present study is the first prospective trial on the efficacy and safety of panitumumab as first-line therapy for patients with WT RAS aged ≥76 or ≥ 65 years who are not considered eligible for intensive chemotherapy. Although, for the frail elderly patients with unresectable CRC, combination therapy with 5-fluorouracil and bevacizumab is a standard care, a cytotoxic regimen is not routinely recommended because of the lack of tolerability. However, the use of panitumumab is expected to be well tolerated and to provide prolonged survival benefit. The present study has some limitations. First, the BRAF mutation is not excluded although the examination of BRAF status was approved in August 2018 in Japan. Second, there is no consideration of tumor location; this is because the efficacy of anti-EGFR monoclonal antibody in right-sided colon cancer was first reported in ASCO 2016 while the protocol of the present study was waiting approval from the ethics committee. Third, the primary endpoint of this study is DCR, although the primary endpoint of a phase II study is generally the response rate. Panitumumab rarely causes severe toxicities, including fatigue or anorexia, especially in frail elderly patients; therefore, panitumumab monotherapy is considered less toxic than capecitabine and bevacizumab combination therapy. Furthermore, the response rate was not high (19%) despite of 74% DCR and a favorable OS with capecitabine and bevacizumab therapy; however, Pietrantonio et al. reported that response rate of panitumumab as first-line therapy was 40% and DCR was 70% [10, 12]. Hence, we decide that the primary endpoint will be DCR. Additionally, in the present study, sarcopenia will be examined as a geriatric assessment, although translational analyses and examination of quality of life are not planned. The findings of the present study will help to establish anti-EGFR monoclonal antibody as the first line of treatment for frail elderly patients with unresectable CRC.

## Data Availability

The datasets used and/or analyzed during the current study are available from the corresponding author on reasonable request.
